## Methods

### Study design

In this multicenter, pragmatic randomized controlled trial (RCT), the protocolized PPEP4All self-management intervention is evaluated against care as usual (CAU) in specialized outpatient mental health care clinics in the Netherlands. Measurements are at 0 (pre-treatment), 3 (post-treatment), 6 (first follow-up), and 12 months (second follow-up), with assessors/data-analysts blind to randomization status. In accordance with current recommendations (in the context of RCTs) [36–41], we use a mixed methods research approach with both quantitative and qualitative data, where the qualitative study is nested in the main RCT project. The qualitative data complements the quantitative data and can facilitate the practical implementation of the intervention, strengthen the clinical relevance of our results, and optimize the PPEP4All intervention by adding the perspectives of patients, partners/caregivers, and clinicians. Moreover, the study protocol conforms to the Standard Protocol Items: Recommendations for Interventional Trials (SPIRIT) guidelines (see Additional file 1).

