### Clinical effectiveness

The mean quality-adjusted life years (QALYs) are estimated using EQ-5D-5L data from four assessments. For the *primary data analysis*, we perform an analysis of covariance for the QALY’s using the post-test EQ-5D-5L results with the pre-test scores as covariate [92–94]. In this way, we test whether there is a difference between PPEP4All and CAU, accounting for the variation where the patients started at the first measurement. For the *secondary data analyses*, secondary parameters are tested using weighted generalized estimating equation (GEE) analyses [97, 98]. Clinical effectiveness analyses are examined using superiority testing.

Moreover, we examine tailored care by further investigating for which groups PPEP4All is the most effective. If possible, subgroup analyses are performed for age, gender, ethnicity, and intervention modality (group/individual). In this context, we explore relevant socio-demographics (e.g., education, living situation, and work) and clinical variables (e.g., comorbidity, baseline severity of disease).

For all outcome analyses, an intention-to-treat (ITT) approach is used, according to the CONSORT statement [99]. Analyses are conducted in SPSS, Stata or R.

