### Economic evaluation

We perform two economic evaluation analyses (see below). The first is a cost-effectiveness analysis (CEA) to determine whether PPEP4All (compared to CAU) is favorably cost-effective at 1-year follow-up. The second is a budget impact analysis (BIA). The economic evaluation is based on the TiC-P questionnaire (see Fig. 2). The TiC-P questionnaire assesses healthcare utilization such as general practitioner (GP) visits and non-healthcare use such as absence from work, reduced efficiency at work, difficulties with job performance (absenteeism from paid work), and production losses without absenteeism from paid work (e.g., presenteeism). Using the area-under-the-curve method for the utility scores results in QALY outcome per patient.

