### Challenges concerning trial recruitment and implementation

We wish to report some early challenges we faced in the recruitment of participants and implementation of our study design and PPEP4All in the participating research centers. After all, patient recruitment is a key determinant of success or failure for clinical trials [127–129].

Firstly, we learned that recruiting only patients with a primary diagnosis of chronic depression/PDD limited our ability to also recruit potential participants with secondary, or comorbid, PDD (e.g., bipolar disorder type II participants with comorbid PDD). After careful deliberation, we allowed these participants to enroll in our study considering that PPEP4All is a generic self-management program that could potentially be used for a wide range of psychiatric disorders and its focus is on recovery, stabilization, and reintegration into the community [130].

Secondly, we had to make the following adjustments to reduce participant drop-out [93]. Initially, we had proposed providing PPEP4All as group treatment, because a group could be the most cost-effective and efficient modality for mental healthcare. However, several patients with PDD preferred individual PPEP4All and therefore refused to participate. This possible preference for individual PPEP4All was also reported to us by the Client Council of the participating centers. For this reason, although PPEP4All is still primarily offered as a group treatment, we also allow the option to provide PPEP4All as an individual treatment (same protocol). In addition, for patients with a preference for group PPEP4All, we lowered the minimum threshold of required group participants to three rather than the original five, which allowed us to start PPEP4All groups without a long waiting period. Moreover, some patients who explicitly wanted PPEP4All withdrew their study participation after they were randomized to CAU. We remedied this with the message that, if necessary, these patients could receive PPEP4All after CAU and completing at least their first or second follow-up.

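### Some CAU patients may receive PPEP4All from month 6, so the 1-year QALY and cost contrast compares PPEP4All with CAU plus optional later PPEP4All

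*Protocol article*

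**What the plan says.** In *Challenges concerning trial recruitment and implementation*, the protocol article reports that "some patients who explicitly wanted PPEP4All withdrew their study participation after they were randomized to CAU". The response was to tell them that, where needed, "these patients could receive PPEP4All after CAU and completing at least their first or second follow-up".

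*Study design* fixes what those visits are. It lists the post-baseline measurements as "3 (post-treatment), 6 (first follow-up), and 12 months (second follow-up". The earliest permitted start of PPEP4All in the CAU arm is therefore just after the month-6 visit.

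The main evaluation runs past that point:

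- *Clinical effectiveness*: "The mean quality-adjusted life years (QALYs) are estimated using EQ-5D-5L data from four assessments".
- *Economic evaluation*: "Using the area-under-the-curve method for the utility scores results in QALY outcome per patient". The aim is to learn whether PPEP4All, set against CAU, "is favorably cost-effective at 1-year follow-up".
- *Cost-effectiveness analysis (CEA)*: costs of PPEP4All and of other care are counted over the first year. An additional analysis extrapolates costs and effects to a lifetime horizon.
- *Clinical effectiveness*, on the analysis set: "For all outcome analyses, an intention-to-treat (ITT) approach is used".

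*Care as usual (CAU)* describes the control arm as mostly long-term supportive care, which patients generally carry on with. It does not mention later PPEP4All.

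**The concern.** A rule stated in one section changes the comparator of a comparison stated in another. Quality of life (through QALYs) and healthcare costs are the primary outcomes. For both, the second half of the 1-year window can include CAU patients who are receiving, or have received, the intervention under test.

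Uptake would not be random. The offer is addressed to patients with an explicit wish for PPEP4All, and it was made because such patients were already leaving.

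Two later steps reuse the same arm. The budget impact analysis takes its costs from the study and includes a scenario in which PPEP4All has not been introduced; a CAU arm containing PPEP4All courses does not estimate that scenario. The lifetime extrapolation carries the mixed comparator forward.

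**Working it through.** **Inputs from the article.** Visits at 0, 3, 6 and 12 months; area-under-the-curve QALY; effect size 0.35; 80% power; 81 per group. The stated alpha of 95% is read as a 5% level.

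**Inputs that are assumptions.** The share p of the CAU arm that crosses over after month 6 (the article gives none; 10%, 30% and 50% are shown); a utility effect d that is zero at baseline and constant from month 3; crossovers reaching the full effect by month 12.

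**The plan's own sample size.** Two independent means with effect 0.35, 80% power and a 5% level need 129 per group two-sided, or 101 one-sided. The stated 81 is reached with ANCOVA only if the baseline-to-outcome correlation is about 0.61 (two-sided) or 0.45 (one-sided); neither is stated. The present point does not depend on this. For the power figures below, the standard deviation is set so that 81 per group gives exactly 80% two-sided power: 0.35 × √(81 / (2 × (1.96 + 0.84)²)) ≈ 0.795.

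**QALY weights.** The intervals are 0.25, 0.25 and 0.5 years. The trapezoid rule gives:

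- month 0: 0.25/2 = 0.125
- month 3: 0.25/2 + 0.25/2 = 0.25
- month 6: 0.25/2 + 0.5/2 = 0.375
- month 12: 0.5/2 = 0.25

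**QALY contrast.**

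- Without crossover: (0.25 + 0.375 + 0.25)d = 0.875d.
- With crossover, the month-12 difference becomes (1 − p)d, and the QALY difference becomes (0.875 − 0.25p)d.
- Fraction retained: q = 1 − (0.25/0.875)p = 1 − 0.286p.

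**Power.** At the calibrated standard deviation, power ≈ Φ(2.80 × fraction retained − 1.96).

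| p | QALY difference lost | QALY power | Month-12 difference lost | Power of a stand-alone month-12 test |
|---|---|---|---|---|
| 0 | 0 | 80% | 0 | 80% |
| 10% | 2.9% | 77.7% | 10% | 71.3% |
| 30% | 8.6% | 72.6% | 30% | 50.0% |
| 50% | 14.3% | 67.1% | 50% | 28.8% |

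The QALY column treats 0.35 as the standardized QALY effect. The last column applies the same effect size to a month-12 test that the article does not name as primary.

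**Costs.** The CAU mean changes by p × (cost of a PPEP4All course − other care it displaces before month 12). The article gives neither term. *Study implications* expects PPEP4All to reduce supportive sessions, so the second term may not be zero and the sign is open.

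**What is unaffected.** Contrasts at months 3 and 6 precede any permitted crossover. If post-test in the primary ANCOVA means month 3, which *Study design* labels post-treatment, that test is also untouched. If every crossover followed the month-12 visit, dilution would be zero.

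**The case against.** The offer is narrow. It concerns only patients who explicitly wanted PPEP4All, and only where needed. The wording leaves open which of the two follow-ups applies. The trial is declared pragmatic, and ITT already settles that crossovers are analysed as randomized. An article may leave supplementary analyses to the full protocol or the analysis plan. Part of the data capture exists: *Assessment and instruments* describes a final survey on modality, number of sessions and PPEP4All adherence, and *Treatment integrity* provides PPEP4All attendance lists and end-of-study information on treatment type within CAU. The offer also has a real benefit, because it was made to stop patients leaving after allocation, and their loss would cost data and risk selective attrition.

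Most of this stands, and it rules out several stronger readings that a reader might infer:

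- *The 1-year comparison is void.* It is not. Randomization and ITT are intact, and the estimate is diluted by an unknown and possibly small amount.
- *The extra cost of PPEP4All is understated.* The documents do not show this. Course costs enter the CAU arm, but other care there may fall.
- *Power drops from 80% to 50%.* That is the month-12 test at an assumed 30% crossover. The primary analysis is an ANCOVA on QALYs, for which the same assumption gives about 73%.
- *The analysis section asserts that CAU stays unmixed to month 12.* It does not say so; it does not mention crossover.

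The objection does not remove the core point. ITT fixes who is analysed in which arm, not which treatments are being compared. The article itself states the rule that mixes the comparator and the 1-year question that presupposes an unmixed one, so this goes beyond detail left to another document.

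**Conclusion.** The point holds as a dilution of the 1-year contrast by a stated rule. Any PPEP4All started in the CAU arm between months 6 and 12 falls inside the four-assessment QALY and the 1-year costs. The ITT estimate then answers a different question from the one in *Economic evaluation*, and the budget impact analysis and lifetime extrapolation inherit that comparator.

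For QALYs the effect is modest: 0.286p of the difference under the assumptions above. The share lost would be larger if the effect grew towards month 12, and smaller if it faded or if crossovers gained less than the full benefit. Secondary outcomes at month 12 are more exposed, losing p. For total costs the direction cannot be stated. The crossover share is the controlling unknown, and the article does not give it.

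**What to change.** 1. Reconcile the offer in *Challenges concerning trial recruitment and implementation* with the 1-year comparison in *Clinical effectiveness* and *Economic evaluation*, including which follow-up the offer refers to. Which rule should apply is for the trial team to decide.
2. Record the start date and sessions of any PPEP4All received by CAU patients, adding to the survey and attendance data already planned. Report how many received it before month 12.
3. Keep ITT as the main analysis, and label the 1-year result as PPEP4All against CAU including crossover.
4. Pre-specify a supplementary 0-6 month contrast of QALYs and costs, which precedes any permitted crossover.
5. Pre-specify a 12-month sensitivity analysis that sets EQ-5D-5L and TiC-P data after crossover to missing and imputes them from baseline and the month-3 and month-6 data. It should not carry the conclusions, because crossovers are selected by preference and no measure of preference is listed among the assessments.

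The cost is one data field and two extra analyses, with an untestable comparability assumption in the second. *Trial status* describes the trial as still recruiting, with its end expected in December 2022, so on that timetable all of this could be settled before analysis.

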## Conclusion

This self-management intervention, PPEP4All, could fill an urgent need in mental healthcare and provide further support for the use of psychiatric rehabilitation via self-management for patients with PDD and their partner/caregiver. Using psychiatric rehabilitation as the next step in the treatment guideline for PDD without remission could replace the non-protocolized usual care and optimize the quality and efficiency of depression care. PPEP4All is expected to reduce costs for the mental health organizations and empower patients to achieve a higher quality of life.

## Trial status

This trial is currently recruiting patients, which started on 1 April 2017 and is anticipated to end on 1 April 2021. The trial is expected to end on 31 December 2022. The protocol is Version 7 dated 1 February 2021.

## Data Availability

Datasets generated and/or analyzed during the current study will be pseudonymized and stored on an online Dutch meta-data catalogue called the Data Archiving and networked Services (DANS, www.dans.knaw.nl), according to the funding sponsor policy, with access limited to a designated team within the Department of Psychiatry of the Leiden University Medical Center. External researchers may get access to the final trial dataset from the designated team on reasonable request. The (intellectual) property rights with regard to the generated data will reside at the Leiden University Medical Center. Anonymized results will be published in peer-reviewed journals and presented in international conferences.

## Abbreviations

B4CZ: Questionnaire on Burden of Chronic Disease, version for Patients or Partners
BIA: Budget impact analysis
BRSnl: Brief Resilience Scale-Dutch translation, 6 items
CAU: Care as usual
CEA: Cost-effectiveness analysis
CEAC: Cost-effectiveness acceptability curve
DANS: Data Archiving and Networked Services
DSM: Diagnostic and Statistical Manual of Mental Disorders
EQ-5D-5L: EuroQoL-5, including the visual analogue scale, 5 items
GEE: Generalized estimating equation
GRP: Good Research Practice research certification
IDS-SR: Inventory of Depressive Symptomatology, Self-Report, 30-items
IMR: Illness Management and Recovery
ISPOR: International Society for Pharmacoeconomics and Outcomes Research-Task Force principles
LUMC: Leiden University Medical Center
MDD: Major depressive disorder
MINI: Mini-International Neuropsychiatric Interview-Dutch translation
NZA: Dutch Healthcare Authority (Nederlandse Zorgautoriteit)
PDD: Persistent depressive disorder
PPEP: Patient and Partner Education Program
PPEP4All: Patient and Partner Education Program for All Chronic Illnesses
QALYs: Quality-adjusted life years
ROM: Routine Outcome Monitoring
SemCAD: Self-Management For Chronic Anxiety and Depression
SPIRIT: Standard Protocol Items: Recommendations for Interventional Trials
SQ-48: Symptom Questionnaire-48, 48 items
SRH: Self-Rated Happiness survey, 1 item
TiC-P: Trimbos Medical Technology Assessment questionnaire for psychiatric illness-associated costs, 30 items
WRAP: Wellness Recovery Action Plan
